#### **OPHTHALMOLOGIC ABNORMALITIES**

Patients who during the study develop blurred vision, decreased visual acuity, photophobia, or eye pain, which are not attributable to another clinical diagnosis (e.g., allergies), should be scheduled immediately for an ophthalmologic evaluation including, but not limited to visual acuity, visual field, color vision, and a dilated fundus exam.

The investigator should contact the Medical Monitor within 24 hours for further discussion.

#### **ANEMIA/DECREASED HEMOGLOBIN**

Refer to Appendix F, [Table F4](#): Dose Adjustment for Low Hemoglobin (Copegus Dose Modification), Appendix F, [Table F5](#): General Copegus Dose Reduction Scheme, and the boceprevir package insert (Victrelis USPI 2011) for dose-modification instructions related to occurrence of anemia or decreased hemoglobin.

## **Appendix G**

### **Management of Specific Adverse Events and Laboratory Abnormalities (cont.)**

#### **NEUTROPENIA**

Refer to Appendix F, [Table F3](#): Dose Adjustment for Low Absolute Neutrophil Count; and [Table F5](#): General Copegus Dose-Reduction Scheme and the boceprevir package insert for dose-modification instructions related to the occurrence of neutropenia or decreased neutrophil count.

## **Appendix H**

### **Urinary Protein Monitoring Plan**

Urine protein/creatinine ratio is a study stopping rule and requires the measurement of urine protein and creatinine concentration. A low urine protein concentration may be physiologic or due to a diluted urine sample caused by a rapid water load prior to voiding.

The methodology used by the central laboratory has a LLOQ of 4 mg/dL. In cases where urine protein is < 4 mg/dL (below the LLOQ), the urine protein/creatinine ratio will be reported by the central laboratory as “Unable to calculate.” To determine a urine protein/creatinine ratio in all patients, the following steps should be taken.

1. On study visit days, patients are required to collect a first void of the day (typically the morning void) urine sample. Concentrations of both urine protein and creatinine will be higher, reducing the risk of undetectable levels and avoiding the variation in protein excretion caused by varying levels of activity during the day. The urine sample should be kept chilled until it is brought to the clinic.
2. In cases where the central laboratory reports a urine protein concentration of < 4 mg/dL (below the LLOQ), the site should calculate the urine protein/creatinine ratio by substituting the LLOQ (i.e., 4 mg/dL) for the urine protein results. The choice of using the LLOQ as the assigned value is a conservative approach when calculating the protein/creatinine ratio. Manual calculation of a urine protein/creatinine ratio will allow assessment of the exclusion criterion, the stopping rule, or the need for additional follow up and will also enable reporting of summary statistics for each visit.

For sites using SI units: To determine if the entry criteria or renal stopping rules have been met, please convert the reported ratio result from SI units to conventional units by multiplying by 0.00884 the result reported in SI units. An example of the conversion of the urine protein/creatinine ratio result from SI to conventional units is as follows:

$$4.52 \text{ mg/mmol} \times 0.00884 = 0.04$$

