#### **4.6.1.1 Discontinuation from Study Drug**

All study medications should be stopped for individual patients for any of the following reasons:

- Hepatitis C virus RNA titer > 100 IU/mL by Week 24
- Quantifiable HCV RNA at Week 24
- Hepatitis C virus RNA virologic breakthrough before the end of treatment with boceprevir and/or RO5024048/placebo and/or Pegasys/Copegus. Virologic breakthrough is defined as:

A sustained increase in HCV RNA of  $\geq 1 \log_{10}$  IU/mL ( $\geq 2$  consecutive measurements) while on boceprevir/RO5024048 compared with the on-treatment nadir (where the nadir is a  $\geq 1 \log_{10}$  IU/mL decrease from baseline after 2 weeks of treatment or  $\geq 2 \log_{10}$  IU/mL decrease from baseline after 4 weeks of treatment)

Confirmed quantifiable HCV RNA ( $\geq 25$  IU/mL by  $\geq 2$  consecutive measurements) in a patient who had been previously confirmed as having unquantifiable HCV RNA ( $< 25$  IU/mL by  $\geq 2$  consecutive measurements) before the end of treatment with boceprevir/RO5024048

Response ( $< 25$  IU/mL by  $\geq 2$  consecutive measurements) to boceprevir/RO5024048 treatment and subsequent quantifiable viral load ( $\geq 25$  IU/mL by  $\geq 2$  consecutive measurements) once boceprevir/RO5024048 treatment has been completed (but Pegasys/Copegus treatment continues)

- Hepatitis C virus partial response before the end of treatment with boceprevir/RO5024048/Pegasys/Copegus/placebo, defined as an initial HCV RNA decline ( $\geq 1 \log_{10}$  IU/mL decrease from baseline after 2 weeks of treatment or  $\geq 2 \log_{10}$  IU/mL decrease from baseline after 4 weeks of treatment) followed by stabilization ( $\geq 2$  consecutive measurements similar to those at nadir) while on boceprevir/RO5024048/Pegasys/Copegus/placebo treatment and/or a HCV RNA  $\geq 1000$  IU/mL by the end of boceprevir/RO5024048/Pegasys/Copegus/placebo treatment of at least 4 weeks in duration
- Any confirmed Grade 4 laboratory abnormality deemed clinically significant (based on the investigator's assessment)
- A positive troponin value ( $> 0.100$  ng/mL)

RO5024048 should be stopped for individual patients for any of the following reasons:

- A creatinine clearance decrease  $\geq 35\%$  from baseline or  $< 60$  mL/min ( $< 1.00$  mL/sec) confirmed by repeat test, preferably within 1 week

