- A urine protein/creatinine ratio  $\geq 0.5$  (56.51 mg/mmol) and greater than the baseline value confirmed by repeat test, preferably within 1 week (see [Appendix H](#))

Refer to [Appendix F](#) and [G](#) for more details on stopping rules and for additional guidance on the management of specific AEs and laboratory abnormalities.

Patients who discontinue study drug prematurely will be asked to return to the clinic for a Study Completion/Early Termination Visit (see Section [4.5.2.3](#)) and may undergo follow-up assessments (see Section [4.5.2.4](#)). The primary reason for premature study drug discontinuation should be documented on the appropriate eCRF. Patients who discontinue study drug prematurely will not be replaced.

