#### **ELEVATED BLOOD PRESSURE/DECREASED RENAL FUNCTION**

During RO5024048 treatment and for 2 weeks thereafter, patients with elevations in systolic blood pressure of > 160 mmHg and diastolic blood pressure of > 100 mmHg confirmed (preferably within 1 week) or increases of 30 mmHg systolic or 20 mmHg diastolic from baseline will be scheduled for weekly blood pressure measurements and laboratory procedures described below.

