## **Appendix G**

### **Management of Specific Adverse Events and Laboratory Abnormalities (cont.)**

During RO5024048 treatment and for 2 weeks thereafter, patients with confirmed (preferably within 1 week) CRCL < 70 mL/min (< 1.17 mL/sec) but  $\geq$  60 mL/min ( $\geq$  1 mL/sec) OR a decrease from baseline  $\geq$  25% but < 35% OR urine protein/creatinine ratio  $\geq$  0.4 ( $\geq$  45.25 mg/mmol) but < 0.5 (< 56.51 mg/mmol) will be scheduled for weekly visits and laboratory assessments described below.

- Blood measurements
  - Complete blood count with differential and peripheral smear for schistocytes
  - Chemistry with calculated creatinine clearance
- Urine panel
  - Urinalysis (dipstick and microscopic)
  - Urine chemistry (first void of the day, chilled sample) for protein, creatinine and microalbumin (for details and calculation of urine protein/creatinine ratio when urine protein is reported as undetectable)

The investigator will use the additional clinical and laboratory measures to evaluate the relationship between elevated blood pressure findings/renal abnormalities and other potential clinical findings and will contact the Medical Monitor within 24 hours for further discussion. All events should be appropriately monitored (including obtaining laboratory test) until resolution or return to baseline.

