## Appendix H

### Urinary Protein Monitoring Plan (cont.)

**Table H1**  
Urinary Monitoring Plan for Protein

| Timepoint           | Finding                                                                    | Action Required by Investigator                                                                                                                                                                           |                                                                                                |
|---------------------|----------------------------------------------------------------------------|-----------------------------------------------------------------------------------------------------------------------------------------------------------------------------------------------------------|------------------------------------------------------------------------------------------------|
| Baseline to Week 24 | Urine chemistry protein/Cr ratio $\geq 0.5$ and greater than the baseline. | Confirm value with repeat urine measurement within 1 week                                                                                                                                                 |                                                                                                |
|                     |                                                                            | IF CONFIRMED:
Discontinue RO5024048 immediately. Collect urine for protein electrophoresis. Continue urine monitoring until protein/Cr ratio returns to baseline or stabilizes. Refer to nephrologist. | IF NOT CONFIRMED:
Continue therapy with RO5024048, continue urine assessments per protocol. |
| Weeks 24–60         | Urine chemistry protein/Cr ratio $\geq 0.5$ and greater than the baseline  | Collect urine for protein electrophoresis. Continue urine monitoring weekly until protein/Cr ratio returns to baseline or stabilized. Refer to nephrologist.                                              |                                                                                                |

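### A urine protein/creatinine ratio of 0.5 or more that does not meet the RO5024048 stop returns to routine testing, while a confirmed 0.4 to below 0.5 brings weekly visits

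*Protocol*

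**What the plan says.** Three places in the protocol act on the urine protein/creatinine ratio.

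- **Stop (Section 4.6.1.1; Table H1, baseline to Week 24).** RO5024048 is stopped for a ratio of at least 0.5 "and greater than the baseline value confirmed by repeat test". If the repeat does not confirm, Table H1 says: "Continue therapy with RO5024048, continue urine assessments per protocol". Its Weeks 24–60 row asks for weekly urine monitoring, but only for a ratio of at least 0.5 that is above baseline.
- **Weekly tier (Appendix G, elevated blood pressure/decreased renal function).** The sentence opens "During RO5024048 treatment and for 2 weeks thereafter, patients with confirmed (preferably within 1 week) CRCL" and goes on to list a ratio of at least 0.4 but below 0.5. These patients "will be scheduled for weekly visits and laboratory assessments described below". The ratio band has no baseline condition. Monitoring runs until resolution or return to baseline.
- **Entry (Appendix H).** Calculating the ratio by hand "will allow assessment of the exclusion criterion, the stopping rule, or the need for additional follow up". Sites using SI units are told to convert "To determine if the entry criteria or renal stopping rules have been met".

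The inclusion and exclusion lists (4.1.1, 4.1.2) contain no urine protein criterion. The renal exclusions are serum creatinine, history of renal disease and creatinine clearance (Nos. 17–19). Appendix A first schedules the ratio at baseline, Day 1; the screening and re-screening cells are empty.

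**The concern.** The upper limit of 0.5 on the weekly tier makes sense only if everyone at 0.5 or above has been stopped. The stop's conditions on baseline and confirmation mean that this is not so, which leaves a band of higher ratios with less ratio-based monitoring than the band below it. A patient who improves from 0.60 to a confirmed 0.45 would move from routine to weekly visits.

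The ratio matters because glomerular toxicity is a nonclinical finding for RO5024048 (Sections 1.2.1 and 5.1). Section 1.2.1 also reports no evidence of clinical renal injury with up to 24 weeks of dosing. What is at stake is the consistency of a safety-monitoring rule for very few patients, plus a cross-reference that sites cannot resolve. No efficacy estimate is involved.

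**Working it through.** **Units.** The worked conversion in Appendix H reproduces: 4.52 × 0.00884 = 0.03996, or 0.04. The tier limits agree: 45.25 × 0.00884 = 0.400 and 56.51 × 0.00884 = 0.4995. Exactly 0.5 would be 0.5 / 0.00884 = 56.56, so the printed 56.51 differs only by rounding.

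**Can a patient enter at 0.5 or more?** Yes. No entry criterion limits the ratio, and it is first measured on Day 1. The stop's wording allows for it too: if baseline is below 0.5, any value of 0.5 or more is automatically above baseline, so the baseline condition has effect only for patients who start at 0.5 or higher.

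**Rules applied as written.** With r the reading, r2 the repeat and b the baseline:

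- weekly tier: 0.4 ≤ r < 0.5, confirmed
- stop: r ≥ 0.5 and r > b, and the same for r2

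| b | r | r2 | As written | With the tier uncapped |
|---|---|---|---|---|
| 0.30 | 0.45 | 0.45 | weekly | weekly |
| 0.30 | 0.55 | 0.55 | stop | stop |
| 0.60 | 0.65 | 0.65 | stop | stop |
| 0.80 | 0.45 | 0.45 | weekly | weekly |
| 0.60 | 0.60 | 0.60 | neither | weekly |
| 0.80 | 0.55 | 0.55 | neither | weekly |
| 0.60 | 0.70 | 0.58 | neither (rise not confirmed) | weekly |
| 0.30 | 0.55 | 0.48 | neither (not confirmed at 0.5) | weekly |

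The last row depends on whether the word *confirmed* in Appendix G governs the ratio as well as creatinine clearance. If it does, 0.55 followed by 0.48 is not a confirmed value in the band, and Table H1 returns the patient to routine testing. If it does not, the 0.48 alone brings weekly visits under Appendix G while Table H1 says routine. The two appendices fail to join up on either reading.

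**Upper bound on extra visits.** Suppose the first on-treatment ratio is at Week 1, it is confirmed at Week 2, and weekly visits run for the whole window (24 weeks of RO5024048 plus 2). Weeks 3 to 26 give 26 − 3 + 1 = 24 visits. Appendix A already has urine tests at Weeks 4, 8, 12, 16, 20 and 24, which is 6. The extra is 24 − 6 = 18. This is a maximum, because Appendix G ends monitoring at resolution or return to baseline.

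**The case against.** The baseline condition in the stop looks deliberate: the sponsor evidently accepted that someone with stable, pre-existing proteinuria may continue. Table H1 is not silent on an unconfirmed rise. Appendix G stops monitoring at resolution or return to baseline, and Table H1, for a confirmed rise, at return to baseline or stabilisation. A patient unchanged at 0.60 is arguably at that point already, so 24 weekly visits is not a realistic comparator. An opposite cure also exists: add an above-baseline condition to the weekly tier, which removes the inverted order at no cost in visits. Few if any patients would enter at 0.5 or more, given the renal exclusions and a total of about 60. For anyone who did, the creatinine-clearance stop and tier remain. So does the blood-pressure trigger, under which patients "will be scheduled for weekly blood pressure measurements and laboratory procedures described below". The ratio is still measured at every scheduled treatment visit, and any confirmed rise, even from 0.60 to 0.61, stops RO5024048.

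Most of this stands, and it limits the size of the point. It does not remove it. A choice to let such patients continue does not explain why a lower ratio should be watched more closely than a higher one. The opposite cure leaves the 0.55-then-0.48 patient unplaced, because 0.55 still lies above the cap.

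A reader might infer that a urine-ratio exclusion was lost and that ineligible patients are being admitted. The documents do not support that: Appendix H states no entry threshold, eligibility is set by Section 4.1, and no screening urine test is scheduled. Nor do they support reading these patients as unmonitored for renal harm.

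**Conclusion.** The gap is real and of low severity. As written, a ratio of 0.5 or more that does not meet the stop gets routine testing only, while a confirmed 0.4 to below 0.5 gets weekly visits. This follows from the wording and needs no assumption about how ratios are distributed. How many patients it touches cannot be derived from the protocol; very few is a judgement, and none is possible. The references in Appendix H to an entry criterion are an editorial error. SVR-12, its confidence interval and the sample size are unaffected.

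**What to change.** 1. In Appendix G, replace the ratio band with: *confirmed urine protein/creatinine ratio ≥ 0.4 (≥ 45.25 mg/mmol) and not meeting the RO5024048 stopping rule in Section 4.6.1.1*. Keep the existing end-points: resolution, return to baseline or stabilisation.
2. In Table H1, have the not-confirmed cell refer to that tier rather than to the routine schedule alone.
3. In Appendix H, delete both references to a urine-ratio entry or exclusion criterion.

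The stop itself does not change, and neither do eligibility, endpoints or sample size. The cost is wording in two appendices and some weekly visits for very few patients: at most 18 each beyond the schedule, and probably far fewer because the end-points would often be reached early.

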## Appendix H

### Urinary Protein Monitoring Plan (cont.)

**Table H1**  
Urinary Monitoring Plan for Protein

| Timepoint           | Finding                                                                    | Action Required by Investigator                                                                                                                                                                           |                                                                                                |
|---------------------|----------------------------------------------------------------------------|-----------------------------------------------------------------------------------------------------------------------------------------------------------------------------------------------------------|------------------------------------------------------------------------------------------------|
| Baseline to Week 24 | Urine chemistry protein/Cr ratio $\geq 0.5$ and greater than the baseline. | Confirm value with repeat urine measurement within 1 week                                                                                                                                                 |                                                                                                |
|                     |                                                                            | IF CONFIRMED:
Discontinue RO5024048 immediately. Collect urine for protein electrophoresis. Continue urine monitoring until protein/Cr ratio returns to baseline or stabilizes. Refer to nephrologist. | IF NOT CONFIRMED:
Continue therapy with RO5024048, continue urine assessments per protocol. |
| Weeks 24–60         | Urine chemistry protein/Cr ratio $\geq 0.5$ and greater than the baseline  | Collect urine for protein electrophoresis. Continue urine monitoring weekly until protein/Cr ratio returns to baseline or stabilized. Refer to nephrologist.                                              |                                                                                                |

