## **PROTOCOL AMENDMENT, VERSION *F***

### **RATIONALE**

Protocol NV27780 has been amended because in the schedule of assessments the Week 42 visit during the treatment phase was accidentally omitted. This omission is addressed in this protocol amendment.

During the design of the protocol it was determined, based on the data from the ongoing HCV studies, that after Week 24 of the treatment phase of the study a visit interval of 6 weeks would be most appropriate to monitor the continued safety and efficacy of treatment with Pegasus®/Copegus® and the experimental drug mericitabine (RO5024048). However, in the schedule of assessments, the Week 42 visit was accidentally omitted.

We are planning to introduce a visit at Week 42, repeating the assessments done at Week 30. After the approval of the amendment, the Week 42 visit will be implemented in the eCRF.

**PROTOCOL AMENDMENT, VERSION F:  
SUMMARY OF CHANGES**

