### Number of Patients

Approximately 60 patients who qualify for the study will be enrolled at approximately 35-40 sites. Patients enrolled prior to protocol version 4 and randomized to Group C will be unblinded and offered mericitabine, in addition to the treatment they are receiving.

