## **4. MATERIALS AND METHODS**

### **4.1 PATIENTS**

Patients enrolled using protocol version 4 will not be permitted to be re-randomized to this study and enrolled for a second course of treatment. Patients who have been enrolled prior to protocol version 4 and randomized to Group C will be offered mericitabine, in addition to the treatment they are receiving. Maximum treatment durations for each component of a patient's regimen will be as follows:

- Boceprevir: 24 weeks (Arm A) or 48 weeks (Arm B)
- RO5024048: 24 weeks maximum
- Pegasys/Copegus: 24 weeks (Arm A) or 48 weeks (Arm B)

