## **4.2 METHOD OF TREATMENT ASSIGNMENT AND BLINDING**

Approximately 60 patients who qualify for the study will be enrolled. Patients will be randomized in a 1:1 ratio. Randomization will be centralized and stratified by HCV genotype (1a or 1b) and by IL28B genetic polymorphism (CC, CT, or TT).

The study is double-blind, and neither study staff, monitors or patients will know which treatment arm individuals have been randomized to.

The randomization list will not be provided to the study center and to the monitors. Patients who have previously been enrolled in Group C will be unblinded and offered mericitabine, in addition to the treatment they are receiving, for a maximum of 24 weeks.

An IMC and safety project team will be unblinded for routine aggregate safety reviews. For purposes of modeling and simulation, drug resistance monitoring, and PK analysis, select members will be unblinded. In order for the Sponsor to make recommendations or decisions regarding further development of the drug, selected members of the project team will have access to the blinding code for interim analyses.

In order to facilitate analysis of the biologic samples collected in this study, the treatment code will be released—according to procedures in place to ensure the integrity of the data—to the responsible analytical person when the samples have been received at the analytical site and are ready for assay. The result of the analysis must not be released with individual patient identification until the database is closed.

If unblinding is necessary for patient management (in the case of a SAE), the investigator will be able to break the treatment code by contacting the interactive voice response system (IVRS). Treatment codes should not be broken except in emergency situations. If the investigator wishes to know the identity of the study drug for any reason, he or she should contact the Medical Monitor directly. The investigator should document and provide an explanation for any premature unblinding (e.g., accidental unblinding, unblinding due to a SAE).

As per health authority reporting requirements, Roche will break the treatment code for all unexpected SAEs (see Section 5.7) that are considered by the investigator to be related to the study drug.

All other individuals directly involved in this study will remain blinded until all patients have completed all study assessments and the database is cleaned and closed.

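### Table H1 confines the proteinuria stop for RO5024048 to Weeks 0–24, but Section 4.6.1.1 sets no week limit and former Group C patients can be on the drug later

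*Protocol*

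**What the plan says.** - **Section 4.6.1.1** lists reasons for which RO5024048 should be stopped in an individual patient. One is a urine protein/creatinine ratio of 0.5 or more (56.51 mg/mmol) "and greater than the baseline value confirmed by repeat test, preferably within 1 week". It gives no study-week limit and points to Appendix H.
- **Appendix H, Table H1** splits the same finding by week. In the row from Baseline to Week 24, the value is repeated and, if confirmed, RO5024048 is discontinued. In the row for Weeks 24–60 the action is: "Collect urine for protein electrophoresis. Continue urine monitoring weekly until protein/Cr ratio returns to baseline or stabilized. Refer to nephrologist". That row has no confirmation step and does not mention RO5024048.
- **Appendix G** attaches its renal monitoring, which includes ratios from 0.4 to below 0.5, to exposure: "During RO5024048 treatment and for 2 weeks thereafter, patients with confirmed".
- **Synopsis, Number of Patients** says that patients enrolled before protocol version 4 and "randomized to Group C will be unblinded and offered mericitabine, in addition to the treatment they are receiving". **Section 4.2** adds the duration: "offered mericitabine, in addition to the treatment they are receiving, for a maximum of 24 weeks". **Section 4.1** repeats the offer and gives "RO5024048: 24 weeks maximum". The amendment rationale shows that mericitabine and RO5024048 are the same drug.

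**The concern.** Table H1 fits patients whose RO5024048 begins on Day 1 and ends at Week 24, because after that there is nothing left to stop. Former Group C patients were already on treatment when RO5024048 was offered, so a full course for them can run past study Week 24. In that period the action column of the table and Section 4.6.1.1 say different things about the same laboratory value.

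This matters because Appendix H calls the ratio a study stopping rule, and because Section 1.2.1 describes glomerular toxicity in monkeys after 13 and 26 weeks of dosing. The list in Appendix F of reasons for immediate RO5024048 discontinuation does not name the ratio. Outside Table H1, the explicit proteinuria stop is therefore the Section 4.6.1.1 item, which sends the reader back to the table. Two sites could act differently on the same result.

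**Working it through.** The protocol states no figure to reproduce here. The check sets the passages side by side and then does the exposure arithmetic.

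**1. Is it the same trigger?** Table H1 uses a ratio of 0.5. Section 4.6.1.1 uses 0.5, or 56.51 mg/mmol. With the conversion factor in Appendix H, 56.51 × 0.00884 = 0.4995, about 0.50. Both also require a value above baseline. The trigger is the same.

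**2. Which week count does Table H1 use?** It does not say. Section 4.5.1 places baseline before any study medication, and nothing restarts the count for Group C. The upper limit of 60 equals 48 treatment weeks + 12 follow-up weeks, and the 12-week follow-up visit is the last urine check in Appendix A. Study week is the natural reading, but it is an inference.

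**3. How much exposure falls in the second row?** Let RO5024048 start at study Week W and run the full 24 weeks, ending at W + 24. Weeks in the second row = (W + 24) − max(24, W), which equals W when W is 24 or less. The start weeks below are assumptions, since the protocol gives none.

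| Start week W | End week | Weeks in second row | Share of 24 weeks |
|---|---|---|---|
| 0 (Groups A and B) | 24 | 0 | 0% |
| 4 | 28 | 4 | 17% |
| 8 | 32 | 8 | 33% |
| 12 | 36 | 12 | 50% |
| 20 | 44 | 20 | 83% |
| 24 | 48 | 24 | 100% |

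For a start after Week 24, all exposure falls in the second row. If all treatment ends by Week 48, a Week 30 start gives 48 − 30 = 18 weeks.

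**4. What do the passages say for a patient on RO5024048 at, say, the Week 30 visit?**

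| Source | Ratio | Clock | Instruction |
|---|---|---|---|
| Appendix G | 0.4 to below 0.5, confirmed | RO5024048 treatment plus 2 weeks | weekly visits and laboratory tests |
| Section 4.6.1.1 | 0.5 or more, above baseline, confirmed | none stated | RO5024048 should be stopped |
| Table H1, second row | 0.5 or more, above baseline | Weeks 24–60 | electrophoresis, weekly urine monitoring, nephrology referral |

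The first two apply to this patient because of the drug being taken. The third is assigned by calendar and lacks both the repeat test and the stop.

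**The case against.** The strongest reply is that the second row is silent, not permissive. The only instruction in Table H1 to continue RO5024048 is in the first row, for a value that was not confirmed. Section 4.6.1.1 covers anyone taking the drug, and Appendix H introduces the ratio as a stopping rule without a week limit. This stands as far as it goes. A reader might infer that the table tells sites to keep dosing, or that no stopping rule exists after Week 24, and the documents support neither. The inconsistency remains, because the column is headed as the action required of the investigator and Section 4.6.1.1 refers to that appendix.

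It is also fair that Group C is a legacy group of unstated size, and that the protocol does not show whether any of its patients are still on RO5024048. That limits what can be said about size. The current text nevertheless keeps the Group C offer in three places, so its safety table should fit those patients.

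The toxicology is not evidence of harm in patients. Section 1.2.1 reports that the monkey findings reversed or were reversing on recovery, and that no clinical renal injury had been seen with up to 24 weeks of dosing.

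Some wider inferences do not hold:
- That RO5024048 could outlast the other drugs in Group C and run beyond Week 48. Section 4.5.2.3 ends all study medication when Pegasys or Copegus stops, and the offer is an addition to ongoing treatment.
- That Section 4.1 gives no RO5024048 maximum for Group C. The 24-week maximum carries no arm label.
- That the Appendix A schedule after Week 24 is defective in the same way. The amendment rationale states that the 6-week interval was chosen deliberately, creatinine clearance stays in every chemistry panel, and no rule on ECGs or same-visit weight is contradicted.

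**Conclusion.** The point holds as a contradiction of limited reach. For any former Group C patient on RO5024048 after study Week 24, Table H1 and Section 4.6.1.1 give different actions for the same ratio, and Appendix G runs on a different clock from the table. Groups A and B are unaffected if their RO5024048 ends at Week 24 as planned.

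For a full course, the exposure affected ranges from 4 of 24 weeks (Week 4 start) to all 24 (Week 24 start). These are illustrations, because the protocol gives neither start weeks nor patient numbers. The conclusion assumes that Group C patients started RO5024048 after Day 1, that Table H1 counts study weeks, and that their other study drugs continue past Week 24. The current text does not state Group C's duration for those other drugs.

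**What to change.** Reconcile Table H1 with Section 4.6.1.1 and Appendix G so that all three give one consistent instruction for any patient still receiving RO5024048 after study Week 24. State in Table H1 which week count applies to former Group C patients. Which action and which clock are right is a clinical decision for the sponsor, and none is proposed here.

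The cost is small: revised wording or a footnote in Table H1, with a matching cross-reference, in the next amendment or a clarification letter to sites. Urine protein/creatinine is already scheduled at Weeks 30, 36, 42 and 48, so reconciling the text does not in itself add an assessment.
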